## Abstract

**Background:**

A 1-session virtual reality (VR) exposure for public speaking anxiety has been found to be effective in reducing public speaking anxiety. Previous meta-analyses comparing 1-session to several sessions of in vivo exposure for specific phobias did not find a difference in effectiveness. However, due to the specificity of VR exposure and public speaking anxiety, it is unclear how dividing the same amount of exposure tasks into 3 shorter sessions instead of one long session would affect the effectiveness of VR exposure for public speaking.

**Objective:**

The aim of this study is to compare the efficacy of a VR exposure-based intervention for public speaking anxiety and the level of VR presence between a 1-session treatment and an equal exposure time divided into 3 sessions, followed by 4 weeks of online intervention in both groups.

**Methods:**

This randomized controlled trial will aim to recruit 86 higher education students experiencing high levels of public speaking anxiety, who will be randomized into one of two conditions: either 1 or 3 sessions of VR exposure therapy, with the same total number of exposure exercises. Both conditions will be followed by the same 4-week online program to encourage in vivo exposure tasks for both conditions. The study will be an exploratory superiority trial testing whether one of the conditions is superior to the other. The primary outcome will be the Public Speaking Anxiety Scale. Assessments will take place pretreatment, at the beginning of the face-to-face session, during the face-to-face session, 1 week after the last VR exposure session, at the end of 4 weeks of the online program, and at two follow-ups at 3 and 12 months after finishing the online program, or equivalent time if the online program was discontinued. Repeated measures within-between ANOVA, the reliable change index (RCI), and effect sizes will be used as statistical analyses, and intention-to-treat will be the primary analysis approach; additional per-protocol analysis will be reported.

**Results:**

The study received funding from the Research Council of Lithuania (LMTLT) in April 2023. Recruitment for the study officially started in January 2024 and was still ongoing during the submission of this paper in December 2025. As of November 2025, a total of 101 participants have completed the initial screening. The final results of the study are expected to be prepared and submitted for publication in March 2026.

**Conclusions:**

This is the protocol of a study that will explore an understudied and clinically important question that could generate preliminary evidence comparing 1-session versus 3-session VR exposure for public speaking and inform further research. However, given the small and specific sample, results would have to be confirmed in larger and more diverse samples.

## Introduction

### Anxiety Disorders and Public Speaking Anxiety

Anxiety disorders are one of the most common mental health problems, with social anxiety disorder (SAD) being found to affect 4%‐12.5% of the general population in their lifetime [1,2]. Social anxiety is the intense fear or anxiety of appearing in front of others (performance), of being observed or judged, or of experiencing shame or public humiliation, and the intensity of the fear causes the individual to avoid threatening social situations and results in disturbances of social, occupational, or other areas [3,4]. Even though many people may experience varying levels of discomfort while speaking in front of others, in severe instances public speaking anxiety may fall under the umbrella of social anxiety disorders in the *DSM-5* (*Diagnostic and Statistical Manual of Mental Disorders* [Fifth Edition]) [3], but it differs from the other SAD subtypes qualitatively and quantitatively, and is therefore distinguished as an independent subtype of SAD [5]. Public-speaking anxiety symptoms can be experienced without SAD, as several previous studies found a much higher lifetime prevalence of significant public speaking fear in community samples (21.2%‐24.8%) compared to the lifetime prevalence of SAD in the same samples (6.6%‐12.1%) [6,7]. However, SAD most often includes a fear of public speaking, with 70.3%‐88.7% of those with SAD also experiencing a significant level of public speaking anxiety [6,7].

Public speaking anxiety is characterized by physiological arousal, negative cognitions, and avoidance or safety behaviors in response to public speaking situations [8]. In cognitive models, public speaking anxiety is caused by negative self-imagery and is associated with overall negative self-perception in social contexts [9]. Individuals with a preexisting negative self-image experience more anxiety in public speaking situations, have more negative thoughts about themselves, and are more critical of their performance [10]. Furthermore, individuals with SAD might have self-imposed high social standards when confronted with an intimidating social situation. They are likely to focus their attention on the anxiety they experience, overestimate the negative consequences of the situation, feel that they have no control over their emotional response, and perceive their social skills as insufficient to cope with the social situation. Public speaking anxiety is furthermore exacerbated by the fear of physiological symptoms [11]. This leads to maladaptive coping—avoidance of engaging in distressing social situations, safety behaviors, and rumination after the event [11]. Avoidance behavior can occur in various contexts and can interfere with adaptation, such as achieving goals in jobs requiring public speaking. For 10% of people, public speaking anxiety causes disruptions in psychosocial functioning or significant distress [12].

### Exposure Therapy for Anxiety Disorders and Public Speaking Anxiety

Exposure therapy has a long tradition of being used for the treatment of anxiety disorders and various phobias [13,14] and has been found to be an effective method for SAD [15] and public speaking anxiety [16] and is often an important part of interventions for public speaking anxiety [17]. Exposure therapy has a variety of forms differing in the structuring of confrontation with the feared situation in the build-up to the intensity of the stimulus, the length of the exposure, and the times in between exposures [18]. Exposure therapy for public speaking anxiety usually involves tasks of giving speeches in front of other people [16]. By continued and repeated exposure to these tasks, a person’s fear response to public speaking should be reduced by the end of treatment. Theories explaining exposure suggest that present anxiety or phobias are a result of an activated fear system, consisting of the feared stimulus, response to it, and meaning of it, which is created by earlier experiences [19,20]. Two main theories slightly diverge in suggesting whether, during exposure, new information showing a lack of threat modifies and extinguishes the existing fear system (the emotional processing model) [19,20] or whether a new safety path, competing with the existing one, is established (an inhibitory learning approach theory) [13,21]. The emotional processing model and an inhibitory learning approach theory are associated with slightly different implications for what processes are the most important during exposure, and sometimes can be traced to different existing traditions and strategies used to maximize exposure therapy effectiveness. Mainly, authors of the inhibitory learning approach, namely, Craske et al [21], criticize the emotional processing model’s emphasis on the need for habituation for the new associations to be created, as previous studies do not confirm that habituation during a session is a good indicator of later fear reduction. Instead, Craske et al [13,21] emphasize the violation of aversive outcome expectations, learning to tolerate anxiety, and the strength of the new association representing safety as more important processes during exposure for more robust long-term exposure therapy effectiveness.

### Virtual Reality Exposure for Public Speaking Anxiety

While exposure therapy is an effective method for anxiety disorders and the process of the method is quite straightforward, the practical execution of exposure in a traditional therapy setting might usually be quite challenging as in vivo exposure is logistically complex [22]. In a traditional therapy session setting, therapists usually will have limited access to patients’ feared stimuli to conduct in-session exposure, even for more common phobias of spiders, dogs, flying, small spaces, etc. This also applies to exposure to public speaking tasks, as setting up an audience specifically for the exposure therapy is ethically and logistically complicated [16]. However, virtual reality (VR) in exposure therapy may help to overcome such limitations. The use of VR is becoming more prevalent in research, as well as in clinical practice [16]. Although less common in the latter setting, the potential of VR seems to be increasing as well, as equipment is becoming more affordable and attitudes of cognitive behavioral therapy clinicians toward VR exposure seem to become more positive [23]. VR addresses ethical and logistical challenges by enabling therapists and patients to work on exposure tasks to a variety of stimuli within the safe and controlled confines of the therapist’s office during regular therapy sessions [24,25]. While there is some discussion about whether exposure in a VR environment can be as effective as in vivo exposure, several meta-analyses showed that VR exposure can be as effective as in vivo exposure for social anxiety disorders [26,27]. A recent meta-analysis [24] found that VR for public speaking anxiety is effective, and another meta-analysis [16] found that while in vivo exposure was slightly more effective, VR exposure was comparably effective to in vivo exposure.

### The Problem of Concentrated vs Spaced VR Exposure Effectiveness

One of the important questions in exposure literature is how to structure exposure to maximize its effectiveness while also optimizing the time and effort demanded from a therapist and a patient. Öst [28] developed a 1-session treatment, an extended 3-hour session with prolonged exposure, primarily aimed at specific phobias. The essential question is whether exposure done in 1 session is as effective as repeated exposure over a longer period of time. Historically, attempts to test the optimal number of exposure sessions and time between sessions for best effects on fear reduction showed mixed results [21]. Different theories would support different strategies for maximizing exposure effectiveness. Traditional habituation and emotional processing theory would emphasize the need for habituation during exposure, which would suggest that longer exposure until a person is no longer feeling anxiety about the stimulus is needed. Öst [29] also describes the development of 1-session treatment based on the idea that a long enough exposure session could achieve full habituation and thus be effective. However, the authors of inhibitory learning theory emphasize that habituation is not necessary and that a more important factor when considering the length and frequency of exposure is maximized variability and unexpectedness of context during exposure to create stronger and more robust new safety associations [13,21]. This would suggest that more frequent exposure in different contexts would be preferable over a prolonged exposure session. Some studies have shown that more than one session showed a better reduction in later fear renewal compared to a 1-session alternative [30,31]. However, a meta-analysis by Odgers et al [32] has found that for specific phobias, a 1-session of in vivo exposure was as effective as treatments with several treatment sessions. As the authors have noted, their meta-analysis was dominated by phobias of animals [32], and as in vivo 1-session treatment has been primarily developed for specific phobias, 1-session exposure treatments might be more suitable for animal phobias than other types of anxiety disorders.

VR exposure introduces an additional dimension to the debate between prolonged and spaced exposure approaches. In VR research, the concept of presence is understood as the extent to which a person connects and engages with the virtual environment [33] or the interpretation of the virtual environment as if it were real [34]. It has been suggested that a sense of presence in a VR environment is necessary for exposure success, as virtual stimuli need to be perceived as real enough to activate the fear system [35]. It might be that presence in a VR environment during exposure might diminish if fear-evoking tasks are performed repeatedly in a short period of time in a single long session. For example, an observed reduction in anxiety might be due to a reduction in presence, but not due to habituation or new safety-representing associations. Factors influencing presence in a VR environment are not widely studied, and the effect of duration in a VR environment on the sense of presence is not clear [36-38]. Research also shows a practical problem of longer VR sessions being associated with increased motion sickness risk [36,39]. This has been found to be associated with increased reaction times and increased heart rate [40], which might negatively impact exposure task effectiveness.

The most commonly mentioned advantage of 1-session treatment is that it offers a clear benefit of saving cost, time, and resources [32]. And of course, for research purposes, the 1-session treatment intervention strategy greatly reduces the issue of participant retention. However, in a traditional therapy setting, a 3-hour session might not be as convenient as suggested, as it is not a traditional time frame for a therapy session; it might be difficult to fit into a regular therapist’s schedule and might require too much time and energy at one time for a therapist and a client. It is possible that the same amount of exposure tasks of one session divided into several sessions might be a more logistically comfortable solution in some settings like traditional therapy or outpatient clinics; however, from previous evidence, it is not clear enough how it would affect the VR exposure for public speaking efficacy.

Due to conflicting theoretical arguments for each condition’s superiority, we hypothesize that the 1-session and 3-session VR exposure for public speaking anxiety will differ in their efficacy without specifying which one will have the superiority. The aim of this study was to compare the efficacy of VR exposure-based intervention for public speaking anxiety and levels of VR presence between two conditions—one-session exposure and the same exposure time divided into 3 sessions, followed by 4 weeks of online intervention for both conditions.

## Methods

### Study Design

The study is a superiority, 2-armed, parallel-group randomized controlled trial. The condition manipulated in the experiment is session spacing—equal VR exposure tasks are either performed in 1 or 3 separate sessions. This protocol follows the SPIRIT (Standard Protocol Items: Recommendations for Interventional Trials) guidelines (Checklist 1).

The study will be conducted in Lithuania. Initial screening for the study and main outcome questionnaires will be completed online. Intake interviews will be done over the phone. The VR exposure part of the intervention will be performed face-to-face on Vilnius University premises. Face-to-face assessments will also be carried out during the in-person session before the start and after the exposure. After the VR exposure sessions, participants will partake in a 4-week online intervention. The participant flowchart is shown in Figure 1.

**Figure 1. F1:**
[figure not shown]
CONSORT (Consolidated Standards of Reporting Trials) diagram for the randomized controlled trial comparing 1-session and 3-session of virtual reality (VR) exposure therapy for public speaking anxiety among young adults.

### Participants and Eligibility Criteria

Participants will be eligible for the program if they meet the following inclusion criteria: (1) young adults aged between 18 and 30 years; (2) students pursuing higher education; (3) a significant level of public speaking anxiety (Public Speaking Anxiety Scale [PSAS] score of 60 or above); (4) access to a computer and internet access for the duration of the study; (5) can understand, write, and speak Lithuanian; and (6) able to participate in 1 or 3 in-person intervention sessions and are able to devote the time to participate in a 4-week online program following the intervention sessions. Participants will be excluded from the study if (1) they have a history of seizures or epilepsy; (2) they have other significant medical conditions that would prevent them from participating in the program; (3) they have high levels of depression (Patient Health Questionnaire-9 [PHQ-9] rating of 15 and above and mentions of suicidal ideation) or other significant psychiatric conditions that would interfere with participation in the program; (4) they have a tendency to have extreme motion sickness reactions or a history of negative physical reactions to VR experiences or difficulty with or lack of stereoscopic vision; (5) they are currently involved in other psychological interventions such as psychological counseling or psychotherapy; (6) they use psychoactive drugs, unless stable for 3 months; or (7) they are currently participating in other programs aimed at reducing public speaking anxiety.

### Sample Size

Sample size was calculated for superiority analysis to test whether one condition shows bigger effects at least at the medium effect level. Power analysis was performed using the G*Power program for repeated measures ANOVA between factors’ effects, which showed that given a significance level of .05 to achieve 80% power to detect a medium between-groups effect (Cohen *f*=0.25) with 2 groups × 3 time measurements (pretreatment, 1 week post last exposure session, and at the end of the online intervention period or equivalent time), with an estimated correlation between repeated factors of 0.5, a total sample of 86 is needed.

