### Statistical Analysis

The primary outcome will be a change in PSAS scores from baseline to posttreatment assessment (two primary endpoints: *t*_2_ and *t*_7_), as well as during follow-up assessments in both intervention groups. Secondary outcomes will be changes in secondary outcome measures from baseline to posttreatment and follow-ups. Repeated measures within-between ANOVA and effect sizes will be used to assess and compare outcomes within and between groups. The reliable change index (RCI) will be used as a supplementary analysis to analyze individual outcomes following intervention. No interim analyses or formal stopping rules were planned because this intervention is considered low-risk and is not expected to cause any harm to the participants. Regression analysis will be used to test the extent to which the level of anxiety and other psychological states measured by primary and secondary measures during baseline, sense of presence (IPQ at the end of the treatment), age, and gender, and user experience rated by participants predict the efficacy of the intervention. Single-item sense of presence after each task and user experience ratings of the format will be used for further exploratory purposes. In order to handle protocol nonadherence and missing data, it is planned that intention-to-treat will be the primary analysis approach, supplemented by additional per-protocol analysis. As recommended by the CONSORT (Consolidated Standards of Reporting Trials) guidelines, both analyses will be performed and reported for primary outcomes [57], allowing comparison of the effects of both approaches. Multiple imputation techniques will be used to fill in missing data.

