## Discussion

### The Importance of Different Formats

This study will aim to test whether 1-session VR exposure effectiveness for public speaking anxiety differs from the same amount of exposure tasks divided into 3 sessions over the period of 2 weeks, while both programs include 4 weeks of online intervention after the exposure sessions. We consider this study to address an important and practical question regarding the optimal arrangement of VR exposure therapy delivery for public speaking anxiety. A few previous studies found that one VR exposure session [25,43] and 4 sessions of VR exposure therapy [42] were effective in reducing public speaking anxiety. However, to our knowledge, no previous study directly compared the same exposure tasks performed in 1 session and divided into 3 sessions in the context of VR exposure for public speaking anxiety. One session of exposure therapy might be convenient in some contexts but also might be too intensive and long for traditional therapy settings. Extended VR usage in a short period of time might also introduce additional disadvantages in a 1-session exposure. On the other hand, 1-session exposure therapy might be convenient in some contexts, where the number of possible appointments is limited. In addition, the chances of discontinued treatment are likely to be higher in multiple VR exposure sessions compared to one session. This study will compare exposure tasks divided into 3 shorter sessions and a 1-session VR exposure treatment. The study will test an understudied and clinically important question that could generate preliminary evidence of 1-session versus 3-session VR exposure for public speaking comparison and would have the potential to inform future research into optimizing VR exposure for public speaking. However, given a quite limited and specific sample, results would have to be confirmed in larger and more diverse samples.

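### The 80% power quoted for 86 participants belongs to an arm difference averaged over time including baseline, not to the primary outcome of change from baseline

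*Protocol article*

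**What the plan says.** All references are to the protocol article.

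- **Sample Size.** The calculation is described as "Power analysis was performed using the G*Power program for repeated measures ANOVA between factors". It claims "80% power to detect a medium between-groups effect" of Cohen f = 0.25 at a significance level of .05. The design is 2 groups by "3 time measurements (pretreatment, 1 week post last exposure session, and at the end of the online intervention period or equivalent time"). The assumed correlation among the repeated measures is 0.5. The result is a total of 86, which is also the recruitment target in the Abstract.
- **Statistical Analysis.** "The primary outcome will be a change in PSAS scores from baseline to posttreatment assessment", with t2 and t7 as the two primary endpoints. The planned method is a within-between repeated measures ANOVA.
- **Primary Outcome Measures** and **Plans for Assessment and Collection of Outcomes.** The baseline PSAS is the online screening score, collected before randomisation.
- **End of the Introduction.** The hypothesis is non-directional: the two formats "will differ in their efficacy without specifying which one will have the superiority".
- **The Importance of Different Formats.** The article expects that "the chances of discontinued treatment are likely to be higher in multiple VR exposure sessions compared to one session". The Limitations section adds that some participants may drop out after one exposure session. The Sample Size section makes no allowance for loss.

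**The concern.** In a within-between ANOVA, the group main effect compares the arms on the average of all the measurements. If one measurement precedes randomisation, its expected arm difference is zero and it dilutes the average. A treatment effect on change from baseline appears instead in the group-by-time interaction, or in the change score at a given endpoint. The sample size is therefore justified for one hypothesis while the primary outcome poses another.

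At stake is how the result is read. A trial that claims 80% power for a medium difference invites the conclusion that a null result makes such a difference unlikely. If the real power for the primary outcome is nearer two in three, that conclusion is too strong.

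**Working it through.** **Inputs from the protocol:** two-sided alpha 0.05, N = 86 (43 per arm, equal allocation), m = 3 measurements, rho = 0.5, f = 0.25. With two equal groups, d = 2f = 0.5.

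**Assumption not in the protocol:** the medium difference d = 0.5 is present at t2 and t7 and is 0 at baseline, with unit variances. The zero at baseline follows from randomisation. The equal size at both post-tests is a reading of the stated medium effect.

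**1. Reproducing 86.** G*Power's between-factors test has noncentrality lambda = f² × N × m / (1 + (m − 1) × rho) = 0.0625 × 86 × 3 / 2 = 8.06 on F(1, 84). Power is 0.801; at N = 84 it is 0.792. So 86 is correct for this test. The interaction option with f = 0.25 would give N = 28, so 86 can only be the group main effect.

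**2. The same test with a zero baseline difference.** The mean difference is (0 + 0.5 + 0.5)/3 = 0.333, so f = 0.167 and lambda = 0.0278 × 86 × 3 / 2 = 3.58. Power is 46%. For 80% power the mean difference must be 0.5, which needs 0.5 × 3/2 = 0.75 SD at both post-tests.

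**3. Group-by-time interaction.** Deviations of (0, 0.5, 0.5) from their mean are (−0.333, 0.167, 0.167), with sum of squares 0.1667. Then lambda = (N/4) × 0.1667 / (1 − rho) = 21.5 × 0.1667 / 0.5 = 7.17 on F(2, 168). Power is 66%.

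**4. Change score at t2.** Variance is 2(1 − rho) = 1, so the standardised difference is 0.5. Lambda = 21.5 × 0.25 / 1 = 5.38 on F(1, 84). Power is 63%. The smallest difference detectable with 80% power is d = 0.61.

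**5. Baseline-adjusted comparison at t2.** Residual variance is 1 − rho² = 0.75. Lambda = 21.5 × 0.25 / 0.75 = 7.17 on about F(1, 84). Power is 75%, and the detectable difference is d = 0.53.

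**6. Sensitivity to the correlation (N = 86, d = 0.5):**

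| rho | Main effect | Interaction | Change at t2 | Baseline-adjusted t2 |
|---|---|---|---|---|
| 0.3 | 55% | 51% | 49% | 67% |
| 0.5 | 46% | 66% | 63% | 75% |
| 0.7 | 40% | 88% | 84% | 89% |

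**7. Sensitivity to loss.** The 15% and 20% rates are assumptions; the protocol gives none. They leave about 73 and 69 analysed. At rho = 0.5, interaction power is 58% and 55%, change-score power 56% and 53%, and baseline-adjusted power 68% and 66%.

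**The case against.** The case for the plan has several parts.

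- **The arithmetic is right, and the text names the between-factors effect and lists pretreatment among the measurements.** This is true, so the fault is in the choice of effect and not in the computation. But the paragraph presents the result as power to show that one format has a medium advantage. A reader is not told that this excludes the primary outcome as defined.
- **The pattern (0, 0.5, 0.5) is not in the document.** Also true, and the figures depend on it. But no randomised design can expect a treatment effect at a pre-randomisation measurement, and that alone breaks the 80% claim for the powered test.
- **The correlation of 0.5 is only an estimate.** This is the strongest point. From roughly 0.65 to 0.7 the interaction and change-score tests reach 80%, so the shortfall for them is conditional. It nevertheless holds at the value the protocol chose and is worse at 0.3. The main effect, which is what was powered, is short of 80% at each of the three values in the table.
- **Discontinued treatment is not missing outcome data, and intention-to-treat with multiple imputation is planned.** Fair; the loss rates are illustrative and the conclusion does not need them. Imputation does not restore the information that is lost, however.
- **The baseline-adjusted figure matches no analysis in the written plan.** Correct; it is shown as the most favourable single-endpoint reading, and at rho = 0.5 it too falls short.
- **The trial is exploratory and the team has already seen data.** The exploratory label does not make an unqualified power statement accurate. Correcting that statement uses no outcome data and alters no analysis.

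**Conclusion.** The concern holds. The figure of 86 is computed correctly for a group main effect averaged over three times including baseline, and the primary outcome is a different effect. On the protocol's own N and correlation, with a medium difference arising only after baseline and no losses, power runs from 46% to 75% depending on the test. The two tests that match the written primary outcome, change score and interaction, have 63% and 66%. None of the four reaches 80%. The shortfall for the change-type tests would disappear at a correlation of about 0.7. The Limitations section concedes other weaknesses of the analysis but does not revisit the power calculation.

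**What to change.** Revise the Sample Size paragraph as follows.

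- Keep the record of how 86 was obtained, but state that the 80% refers to the arm difference averaged over pretreatment, t2 and t7, and does not apply to change from baseline. Otherwise delete the 80% claim.
- Add power for the arm difference in PSAS at t2, which the Limitations section now treats as the main primary endpoint. With 86 analysed and rho = 0.5, d = 0.5 has 63% power as a change score, or 75% if the comparison is baseline-adjusted. The differences detectable with 80% power are d = 0.61 and d = 0.53.
- Show how these figures move with the correlation, and repeat them for an assumed loss to follow-up labelled as an assumption.
- Because data have been seen, date the addition and mark it as a clarification.

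The cost is the wording of one paragraph and a less favourable power statement. No participants are added and no analysis changes.

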### Limitations

There are several limitations and risks that we anticipate during the trial. First of all, exposure therapy, by the nature of the method, induces anxiety and discomfort. Participants might be more reluctant to participate in the study and drop out after one exposure session. There will be a need to evaluate the discomfort level of the participant and encourage continuation of the exposure even when they experience discomfort; however, in severe cases of negative reactions, exposure will be discontinued. Another problem we anticipate is participants’ reluctance to continue a transition to in vivo exposure during 4 weeks of online intervention. Low compliance was reported in the equivalent program after VR exposure in the previous study by Lindner et al [43]. To increase compliance, we will ask participants to confirm they will be able to participate in the 4-week online program after the exposure by emphasizing the importance and rationale of online intervention during the in-person session. Another limitation is that although we will measure presence and hypothesized that the length of the sessions might be related to cybersickness for some, for a more parsimonious design of the study, other than excluding participants who reported a history of strong motion sickness, we will not explicitly measure and test motion sickness during VR exposure sessions, which could be one of the confounders of the exposure effectiveness between the different conditions. Due to a very specific and convenient sampling strategy in this research, generalization of the obtained results is strictly limited to young adults pursuing higher education and cannot be directly applied to clinical populations or people from other age groups or social categories. Yet another limitation is that this research focuses on the comparison of different delivery methods with the same amount of VR exposure followed by an online program. Since it does not include a control group that does not have an active intervention, this research is not testing whether this VR exposure therapy is more effective than no treatment, treatment as usual, or a stand-alone online program, but explores comparative efficacy.

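### The recruitment target of 86 is the complete-data minimum for 80% power, so any lost t2 or t7 outcomes take power below the stated figure

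*Protocol article*

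**What the plan says.** The Sample Size section describes a G*Power calculation for "repeated measures ANOVA between factors’ effects", with 2 groups, three measurements (pretreatment, 1 week after the last exposure session, and the end of the online period), Cohen f of 0.25 and a correlation of 0.5 between measurements. The criterion is "given a significance level of .05 to achieve 80% power", and the conclusion is that "a total sample of 86 is needed". The section mentions neither attrition nor missing outcomes.

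The Abstract uses that number as the target: "This randomized controlled trial will aim to recruit 86 higher education students".

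Elsewhere the protocol foresees loss. Limitations lists this among the anticipated risks: "Participants might be more reluctant to participate in the study and drop out after one exposure session". It also expects reluctance to continue during the online phase. The Discussion section on the importance of different formats says that "the chances of discontinued treatment are likely to be higher in multiple VR exposure sessions compared to one session". Statistical Analysis makes intention-to-treat the primary approach and plans multiple imputation for missing data. No section gives an expected loss rate.

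**The concern.** The number needed and the number to be recruited are the same. If the calculation assumes that everyone supplies all three assessments, the 80% holds only if nobody's t2 or t7 outcome is lost, and the protocol does not expect that.

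What is at stake is how the result is read. The hypothesis is that the two formats "will differ in their efficacy without specifying which one will have the superiority". A non-significant comparison judged against a nominal 80% would invite the conclusion that spacing makes no difference, with more assurance than the design gives.

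**Working it through.** **Inputs (Sample Size section).** Groups k = 2; measurements m = 3; correlation ρ = 0.5; f = 0.25; α = 0.05. The hypothesis is non-directional, so the F test is used as it stands. Allocation is equal (Assignment of Interventions: Allocation).

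**Formula.** For the between-factors test in a repeated measures ANOVA, power comes from a noncentral F distribution with df 1 and N − 2 and noncentrality

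λ = N f² m / (1 + (m − 1)ρ) = N × 0.0625 × 3 / 2 = 0.09375 N.

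**Step 1: reproduce the plan's figure.**

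| N with complete data | λ | Power |
|---|---|---|
| 84 | 7.88 | 79.2% |
| 85 | 7.97 | 79.7% |
| 86 | 8.06 | 80.15% |

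The plan's 86 is reproduced. It is the smallest N that reaches 80%, so no attrition allowance can be hidden in it. One participant fewer is already below 80%.

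**Step 2: 86 recruited, only completers contribute.** The loss rates are assumptions, because the protocol gives none. Numbers are rounded to whole participants.

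| Assumed loss | Completers | λ | Power | f detectable with 80% power |
|---|---|---|---|---|
| 0% | 86 | 8.06 | 80.1% | 0.25 |
| 10% | 77 | 7.22 | 75.6% | 0.26 |
| 20% | 69 | 6.47 | 70.8% | 0.28 |
| 30% | 60 | 5.63 | 64.5% | 0.30 |

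**Step 3: favourable bound.** Suppose all 86 keep their baseline, a fraction d lose both t2 and t7, and the group effect is constant over the three times. A participant with all three measurements contributes information 3/(1 + 2 × 0.5) = 1.5, and one with baseline only contributes 1. Then

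λ = 86 × 0.0625 × [1.5(1 − d) + d] = 5.375 × (1.5 − 0.5d), with df 1 and 84.

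| Assumed loss d | λ | Power |
|---|---|---|
| 10% | 7.79 | 78.8% |
| 20% | 7.53 | 77.4% |
| 30% | 7.26 | 75.9% |

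This is generous, because it credits the pre-randomisation baseline with information about the group effect. Power is still below 80% at each of these rates.

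**The case against.** **No stated figure is wrong.** This is true. The 86 follows from its inputs, and the Abstract states the target without attaching a power to it. The article also condenses a fuller document. The point rests on the two statements taken together: the complete-data minimum is also the recruitment target, in a plan that anticipates dropout and missing data.

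**Stopping treatment is not losing outcomes.** This stands, and it narrows the point. A reader might infer from the expected higher discontinuation with several sessions that the 3-session arm will lose data at that rate. The documents do not support this. That sentence concerns treatment. The footnotes to Table 1 schedule t7 and both follow-ups at an equivalent time for those who stop the online program. Outcomes after baseline are completed online, with email reminders followed by a phone call, and intention-to-treat is primary. Someone who stops early but completes t2 and t7 costs no observations. The dropout remark in Limitations is itself worded as a possibility.

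**Completers-only figures are pessimistic.** This also stands. The primary analysis is intention-to-treat with multiple imputation, which can recover part of the information through the baseline and any observed assessment. It cannot replace outcomes that were never observed, so both ends of the range need to be shown.

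**The planned within-between analysis may test a different effect.** G*Power's interaction option with the same inputs needs only 28. But f has a different meaning there, so this does not show that the trial is well powered. Which effect should have been powered is a separate question. The present point accepts the plan's chosen test.

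**The trial is called exploratory and its evidence preliminary.** This limits the harm, but it does not make the 80% correct for 86 recruited.

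**Conclusion.** The point holds in limited form. Recruiting 86 delivers the stated 80% on the plan's own between-factors test only if no t2 or t7 outcome is lost. The direction is clear. The size is not known, because the protocol gives no loss rate. For assumed losses of 10% to 30%, the shortfall from 80.1% is about 1 to 4 percentage points under the favourable bound and about 5 to 16 points if only completers contribute.

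A reader might take 65% as the trial's power. That requires both a 30% loss of outcomes and an analysis that discards everyone affected, and the plan says neither. A reader might also bring in the 37 participants randomised by November 2025. That is an interim count with recruitment still open. It is a separate recruitment matter and says nothing about attrition.

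**What to change.** Do not enrol more participants. Restate the figure:

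- In the Sample Size section, say that 80% power applies to 86 participants with complete pretreatment, t2 and t7 data.
- Add that if 86 are recruited and 10%, 20% or 30% lack outcomes (labelled as assumptions), power is about 76%, 71% or 65% with completers only, and about 79%, 77% or 76% under the favourable bound.
- In the results report, give the detectable effect for the number actually assessed, and interpret the primary comparison from its confidence interval rather than against a nominal 80%.

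The cost is a few sentences and a less favourable power statement. Conduct and analysis do not change. Limitations says that the team has already worked with the data, and a restatement of this kind does not conflict with that.
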